### Randomization

Subjects are randomly assigned to the intervention or control group, stratified by 25-OHD, age, and sex using the Randomizer for Clinical Trials 1.8.1 online tool [64]. Each subject receives an appropriate randomization number. Randomization is carried out after the patient has signed the informed consent form and before undergoing bariatric surgery, right before the baseline assessment. Allocation to the groups is performed with consecutively numbered dark bottles containing either vitamin D_3_ (cholecalciferol) or placebo (carrier oil). These allocation bottles are labeled with the randomization number.

### Intervention

#### Loading dose determination

A loading dose is an extent of drug or substance designed to fill the central volume of distribution to a concentration that matches the final plateau concentration achieved with the maintenance dose. Consequently, this final plateau could be achieved sooner than the four half-lives required if it is administered only at the maintenance dose rate [65]. According to the current guidelines, a minimal daily vitamin D supplementation of at least 3000 IU is recommended [23]. To prevent failure of the study due to an insufficient treatment dose, we chose the maximum loading dose for which sufficient safety data are available. The functional half-life for vitamin D_3_ in the body is between 2 and 3 months [66–68]. As a result, the loading dose can be calculated as the cumulative maintenance dose that is planned to be given through one functional half-life of vitamin D, as follows:$$ \mathrm{Loading}\ \mathrm{dose}=\left(\mathrm{daily}\ \mathrm{maintenance}\ \mathrm{dose}\ \mathrm{of}\ 3420\ \mathrm{IU}\right)\times \left(90\ \mathrm{days}\right)=307,800\ \mathrm{IU}\left(\mathrm{total}\ \mathrm{loading}\ \mathrm{dose}\right) $$

In previous studies, researchers used doses exceeding this dosage, at 500,000 and 600,000 IU of cholecalciferol/vitamin D_3_ in frail elderly patients, young patients, and critically ill patients, without observing any adverse effects (e.g., hypercalcemia) [66, 69, 70]. The total loading dose of 300,000 IU is given on the basis of the measured 25-OHD blood levels and/or concentrations (except for the first dose, given at day 1 after surgery, of 100,000 IU) up to a maximum of 300,000 IU. To make the loading dose protocol safer, 100,000 IU of vitamin D is administered at one time to allow clearance from the circulation between each increment of the loading dose [71].

According to the European Food Safety Authority (EFSA), the no observed adverse effect level was established at 10,000 IU per day and the tolerable upper intake level (UL) at 4000 IU per day (based on induction of hypercalcemia as the indicator of toxicity) [72, 73]. The maintenance dose, given after the loading dose, is 3420 IU per day, which is in accordance with the EFSA panel guideline of a UL of 4000 IU per day [72]. Taken together, no harm or risk is expected for patients in the intervention and placebo groups. Importantly, as a result, appropriate selection of maintenance and loading doses can reduce the need for follow-up monitoring of 25-OHD levels.

#### Intervention group

The oral loading dose of 300,000 IU cholecalciferol (vitamin D_3_) is divided into three doses (100,000 IU each) and is given on day 1 and at 2 and 4 weeks postoperatively. The oral maintenance dose is given up to 24 weeks and until the follow-up visit (46 weeks). All patients in the intervention group receive the first loading dose. The second and third doses are given based on the 25-OHD serum concentration, which is assessed before administration. If the 25-OHD does not reach a level above 75 nmol/L, a 100,000 IU dose is again given, up to 300,000 IU in total. After the last loading dose, a maintenance dose of 3420 IU per day (approximately translating to 60 drops and 24,000 IU per week) should maintain the high 25-OHD concentration, according to guidelines (Fig. 2) [23].

**Fig. 2 Fig2:**
[figure not shown]
Dosing regimen. [25 - OHD 25-hydroxy vitamin D]

#### Placebo group

The carrier solution (medium-chain triglyceride oil [MCT]), of the verum formulation (MCT + vitamin D) is used in the placebo-only group. The placebo group is treated exactly the same as the intervention group (Fig. 2).

### Measurements

Patient history and dietary assessment data are documented at baseline and collected four times. For all subjects, body weight, body composition, and blood parameters are assessed eight times. The liver function assessment is done four times. Blood pressure, depression symptoms, BMD, and total body fat mass are measured two times in all study groups. The visit and assessment schedule are shown in Fig. 3 and Table 1.

**Fig. 3 Fig3:**
[figure not shown]
Flowchart. [BMD bone mineral density]

The measurements to be performed are described in the subsections below and in Table 2.

#### History, blood pressure, and dietary assessment

Medical history, such as comorbidities, prescribed medications, and demographics (marital status, education, migration background, and career)Blood pressure (mmHg)Dietary assessment to provide information regarding dietary vitamin D intake as follows:*5*-*day food record*: During the week before the scheduled visit, patients should record their food intake for 5 days. Data are analyzed using the nutritional software nut.s, which is based on Bundeslebensmittelschlüssel (Max Rubner-Institut; http://www.bls.nvs2.de/).*Mediterranean Adherence Score*: A brief, validated questionnaire regarding adherence to the Mediterranean diet results on a 14-point scale [74]; the higher the score, the better the adherence to the proposed diet

#### Anthropometry

Weight (kg), measured with a calibrated scaleHeight (cm), measured with a wall stadiometerWaist circumference, measured with an inelastic tape*Body composition*: fat-free mass, lean body mass, total body water, and phase angle are assessed by bioelectrical impedance analysis (BIA) [75], based on the transfer of a low-voltage alternating current through the body. This measurement captures the voltage drop of the applied current and result in measuring resistance and reactance. It is used with height, weight, age, and sex in a number of multiple regression relationships to calculate body composition compartments [76]. A single frequency BIA at 50 kHz and 0.8 mA (Biacorpus RX 4000; MediCal HealthCare GmbH, Karlsruhe, Germany) is passed between electrodes (Bodystat, Isle of Man, UK) placed on the dominant side hand and foot with patients in the supine position.

#### Stage of liver stiffness and steatosis

Transient elastography FibroScan (Echosens, Paris, France) with a controlled attenuation parameter (CAP™) will be performed based on transmitting a vibration signal into the liver and receiving the resulting shear wave, which depends on liver stiffness. CAP™ measures ultrasonic attenuation in the liver at 3.5 MHz and detects liver steatosis.

#### Bone mineral density and total body fat mass

Dual-energy X-ray absorptiometry (DEXA) will be used to measure bone mineral content, BMD, and percent body fat.

#### Laboratory parameters

*Vitamin D status*: 25-OHD (nmol/L), 1,25-dihydroxy vitamin D (pg/ml)*Biochemical parameters*: sodium (nmol/L), potassium (nmol/L), chloride (nmol/L), calcium (nmol/L), magnesium (nmol/L), iron (μg/dl), total protein (g/L), albumin (g/L), triglyceride (mg/dl), total cholesterol (mg/dl), high-density lipoprotein (mg/dl), low-density lipoprotein (mg/dl), vitamin B_12_ (pmol/L), folic acid (nmol/L), vitamin A (μmol/L), vitamin E (μmol/L), ferritin (μg/L), transferrin (mg/dl), and transferrin saturation (%)*Bone turnover markers*: calcium (mmol/L), osteocalcin (ng/ml), bone-specific alkaline phosphatase (U/L), type I collagen cross-linked C-terminal telopeptide (ng/ml), anorganic phosphate (mmol/L), parathyroid hormone intact (pg/ml), and amino-terminal propeptide of type I procollagen (ng/ml)*Inflammation markers*: C-reactive protein (mg/dl) and interleukin 6 (pg/ml)*Insulin resistance markers*: C-peptide (ng/ml), insulin (μU/ml), blood glucose (mg/dl), and glycosylated hemoglobin HbA1c (%)*Liver parameters*: aspartate transaminase (U/L), alanine transaminase (U/L), γ-glutamyl transpeptidase (U/L), total alkaline phosphatase (U/L), and cholinesterase (U/L)Blood count*Coagulation*: Normotest (%) (Technoclone, Vienna, Austria), activated partial thromboplastin time (s), and fibrinogen (mg/dl)*Protein electrophoresis*: serum protein electrophoresis, haptoglobin (mg/dl), and α_2_-macroglobulin (mg/dl)

#### Depression symptoms

The Beck Depression Inventory (BDI) [77] (simplified BDI-V), a 21-question, multiple-choice, self-report inventory will be used for measuring the severity of depression [78].

#### Microbiota composition

Stool samples will be collected to evaluate changes in the composition of intestinal microbiota resulting from weight reduction and vitamin D supplementation.

#### Biopsy

For the purposes of describing adipose depot vitamin D concentrations and expression of enzymes in SAT, visceral adipose VAT and liver tissue samples are collected by the surgeon during surgery. Furthermore, liver tissue samples are used, in addition to the prescribed study-related measures, for histological examination as extended diagnostics. Samples are snap-frozen in isopentane and stored in nitrogen tanks at −196 °C until assayed. Biopsies will be performed as follows:*Adipose tissue*: The SAT sample is extracted through a linear incision in the abdominal wall with no additional incision. The VAT sample is taken from the greater omentum, coming off the transverse colon.*Liver tissue*: Standard intraoperative wedge and needle biopsies are collected during surgery.

### Statistical analysis

Data exploration using descriptive statistical analysis and inferential statistics (uni- and multivariate) will be performed. The data will be described by frequencies or percentages, means and standard deviations, medians and confidence intervals, and graphics. For proofing of normal distributions, visual inspection of histograms or box plots will be used. Independent samples *t* tests, Mann–Whitney *U* test or *χ*^2^ tests will be performed to compare groups. Correlation coefficients will be used with respect to the secondary outcomes. Analysis of covariance will be used to compare parameters at baseline and after the intervention (postoperatively), as well as after the follow-up, between intervention and control groups, adjusting for the baseline value as a covariate. IBM SPSS Statistics for Windows version 22 software (IBM, Armonk, NY, USA) will be used for all statistical analyses. All tests are two-sided, and a *p* value <0.05 is considered statistically significant.

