## Methods/Design

### Overview

This prospective, double-blind, randomized controlled intervention trial includes administration of a vitamin D loading dose and repeat doses in patients undergoing bariatric surgery. A stratified randomization design is being used to obtain comparable groups to ensure that baseline variables (25-OHD, age, and sex) are evenly distributed between groups. Subjects are randomly assigned to the intervention or control group. In this study, 50 bariatric patients planning to undergo OLGB will be recruited. Over the first month postoperatively (day 1–3, weeks 2 and 4), they will receive the loading dose of vitamin D. Afterwards, the maintenance dose will be given up to 24 weeks and until the follow-up visit. An overview of the study design and the assessment points is provided in Fig. 1. The study was approved by the local ethics committee of the Medical University of Vienna (reference number 1899/2013) by the Austrian Competent Authority (reference number LCM-718280-0001), and it complies with the Declaration of Helsinki [57]. Furthermore, the protocol was registered at ClinicalTrials.gov (identifier: NCT02092376) and EudraCT (identifier: 2013-003546-16). The study methods are in accordance with the 2010 Consolidated Standards of Reporting Trials (CONSORT) Statement guidelines for reporting randomized trials [58].

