### Sample size calculation

The study is powered to detect differences among the groups for 24-week serum 25-OHD levels. On basis of the preevaluation (cohort study), the placebo group was conservatively estimated to have an average 24-week 25-OHD level of 50 ± 30 nmol/L. For sample size calculation, the difference in 25-OHD levels between groups will be considered. Given a clinically relevant difference of 30 nmol/L and a standard deviation of 35 nmol/L of the differences, a two-sided significance level of 0.05, a sample size of 22 per group is needed to reach 80 % statistical power. Because imputation for dropouts of 20 % may have some inestimable effect on the assumed standard deviation of the differences, the sample size is increased to 25 per group. To reach this sample size, a total of 50 bariatric patients in the study are needed. The primary endpoint will be analyzed according to the intention-to-treat principle.

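### Randomization is stratified by 25-OHD, age and sex, but the stated analyses leave out some or all of these factors, so the test is mildly conservative and a little precision is lost

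*Protocol article*

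**What the plan says.** The Overview of the protocol article gives the purpose of stratifying: "to ensure that baseline variables (25-OHD, age, and sex) are evenly distributed between groups". The Randomization section repeats the three factors: allocation is "stratified by 25-OHD, age, and sex using the Randomizer for Clinical Trials 1.8.1 online tool". Cut-points, block size and algorithm settings are not given.

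The Statistical analysis section lists independent-samples t, Mann-Whitney U and chi-square procedures and says these "tests will be performed to compare groups". It then describes an analysis of covariance of post-intervention and follow-up values "between intervention and control groups, adjusting for the baseline value as a covariate". It does not say which of these is the primary analysis. A general mention of univariate and multivariate methods names no covariates, and age and sex are placed in no model.

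The Sample size calculation section fixes the endpoint: "The study is powered to detect differences among the groups for 24-week serum 25-OHD levels". Its calculation is an unadjusted comparison of two means for a difference of 30 nmol/L and an SD of 35 nmol/L, tested two-sided at 5%. It concludes that "a sample size of 22 per group is needed to reach 80 % statistical power". The number is then raised to 25 per group.

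**The concern.** Stratified allocation removes much of the chance imbalance in the factors, so the treatment estimate varies less from trial to trial. A test that omits the factors does not see this. It still counts the variance they explain as residual noise and reports a standard error for an unstratified trial. If the factors predict the outcome, confidence intervals are wider than they need be, the true type I error lies below 0.05, and some power is lost.

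At stake is precision in a trial of 50 patients. The sponsor judged the three factors important enough to balance, but the stated covariate rule takes up one of them at most for the primary endpoint. For a secondary outcome, the baseline value is that outcome's own baseline, so the ANCOVA may use none of them.

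**Working it through.** **Inputs from the protocol article.** Difference 30 nmol/L, SD 35 nmol/L, two-sided alpha 0.05, power 80%, 22 per group raised to 25, three stratification factors.

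**Assumed, because not given.** R-squared of baseline 25-OHD and of age plus sex for week-24 25-OHD; 2 x 2 x 2 = 8 strata; permuted blocks of 4; 25% of patients in the smaller sex category.

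**Step 1: the plan's own figure.** n per group = 2 x (1.96 + 0.84)^2 x 35^2 / 30^2 = 21.4, rounded up to 22. The stated figure is reproduced and contains no covariate or stratification term. At 25 per group the unadjusted t test has 84.4% power (noncentral t).

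**Step 2: the mechanism.** The t test reports a standard error of about 35 x sqrt(2/25) = 9.90. If stratification balanced all explained variance perfectly, the true standard error would be 9.90 x sqrt(1 - R2), and the true type I error would be 2 x P(Z > 1.96 / sqrt(1 - R2)). That gives 3.9%, 2.8% and 1.9% for R2 = 0.1, 0.2 and 0.3. Stratifying on categories of age and 25-OHD balances less than this, so these values bound the effect and do not estimate it.

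**Step 3: standard errors by simulation** (50 patients, no treatment effect, 2,500 trials). R-squared is written as baseline 25-OHD / age plus sex.

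| R-squared | Allocation | t test: true SE, reported SE | Baseline ANCOVA: true SE, reported SE |
|---|---|---|---|
| 0.10 / 0.05 | stratified | 9.56, 9.81 | 9.35, 9.36 |
| 0.20 / 0.10 | stratified | 9.04, 9.85 | 8.67, 8.84 |
| 0.20 / 0.10 | unstratified | 9.81, 9.83 | 8.96, 8.89 |

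At 0.20 / 0.10 the t test overstates its standard error by 9.85/9.04 - 1 = 9%, and the baseline ANCOVA by 8.84/8.67 - 1 = 2%. Without stratification, true and reported values agree to within simulation error. The excess therefore comes from stratifying and then not adjusting.

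**Step 4: type I error** (stratified, 6,000 trials, Monte Carlo error about 0.3 points).

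| R-squared | t test | Baseline ANCOVA | All three factors |
|---|---|---|---|
| not prognostic | about 5% | about 5% | about 5% |
| 0.10 / 0.05 | 3.8% | 4.7% | 5.3% |
| 0.20 / 0.10 | 3.2% | 4.0% | 4.6% |
| 0.20 / 0.18 | 2.8% | 3.3% | 5.0% |

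Minimization instead of blocks gives similar or slightly stronger conservatism (2.6% and 3.8% for t test and baseline ANCOVA at 0.20 / 0.10).

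**Step 5: power for 30 nmol/L, SD 35, 25 per group, no dropout** (5,000 to 6,000 trials).

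| R-squared | t test | Baseline ANCOVA | All three factors |
|---|---|---|---|
| not prognostic | 84% | 84% | 83% |
| 0.10 / 0.05 | 85% | 88% | 89% |
| 0.16 / 0.05 | 86% | 90% | 91% |
| 0.16 / 0.10 | 86% | 90% | 92% |
| 0.25 / 0.18 | 87% | 94% | 97% |

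Most of the gain over the t test comes from baseline 25-OHD, which the stated ANCOVA already includes. Age and sex add 1 to 3 points in these settings.

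**The case against.** The strongest reply has four parts.

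- **The main factor is already covered.** For the primary endpoint the baseline value is baseline 25-OHD, itself a stratification factor and plausibly the most prognostic. This stands. A reader might infer that the trial throws away the benefit of stratification altogether. That would be true only if the t test or Mann-Whitney test were the primary analysis, and the article does not say so.
- **The size rests on assumed R-squared values.** This also stands. Nothing in the document shows that age or sex predicts week-24 25-OHD here. At 5% for the two together, the baseline ANCOVA is close to nominal; at zero there is nothing to gain.
- **The trial is not left underpowered by this.** A reader might infer that the omission takes the trial below 80% power. At the protocol's own effect (30/35 = 0.857 SD) and 25 per group, every method in the working exceeds 80%. With 20% dropout and 20 completers per group, an unadjusted t test has 75% power. That shortfall belongs to the sample size, not to the covariates. The baseline ANCOVA then has 82% to 86% with a baseline correlation of 0.4 to 0.5, and about 79% at R-squared 0.10 / 0.05. Power quoted at a smaller standardized effect would have no basis in the document.
- **An article condenses, and a separate analysis plan may list more covariates.** If that plan already includes age and sex, the point falls away. But the article is not silent: it states a covariate rule, and that rule names only the baseline value.

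**Conclusion.** The mismatch between design and stated analysis is real and its direction is certain whenever the factors are prognostic: the standard error is overstated and the test is conservative. A reader might infer a threat to validity. There is none, because the estimate stays unbiased and alpha is not inflated.

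The size is modest and assumed. Under the ranges examined, the t test runs at roughly half to four fifths of the nominal 5%. The baseline ANCOVA lies closer to nominal, and adding age and sex to it gains no more than about 4 points of power. The loss may be relatively larger for secondary outcomes, where none of the three factors need be in the model; this was not quantified. The point is minor and is best treated as a nearly free improvement.

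**What to change.** Name one primary analysis: an ANCOVA of week-24 25-OHD on treatment, baseline 25-OHD (continuous), age (continuous) and sex. Keep the t test or Mann-Whitney test as a sensitivity analysis. In the secondary ANCOVAs, add the three stratification factors alongside the outcome's own baseline. Record the change before unblinding.

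The cost is one or two sentences and no new data, since all three variables are needed for randomization. The primary model loses 2 degrees of freedom (50 - 3 = 47 becomes 45), which costs about 1 point of power if age and sex turn out not to be prognostic.

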Obesity is frequently characterized by reduced vitamin D bioavailability, insulin resistance, and a chronic inflammatory response. There is a relationship between serum concentrations of 25-hydroxy-vitamin D (25-OHD) and several circulating inflammatory markers in severely obese individuals [31]. This observed relationship between low vitamin D status and obesity may be caused by mechanisms such as sequestration in adipose tissue. The mechanisms underlying the inverse relationship between obesity and vitamin D deficiency are largely unknown. Low serum 25-OHD might contribute to obesity by affecting lipogenesis and/or adipogenesis in the adipose tissue. Interestingly, recent studies [32] suggest that the adipose tissue could be a direct target of vitamin D and that the hormone may modulate adipose tissue formation and function [33–37].

Obesity has recently been associated with non-alcoholic fatty liver disease (NAFLD). NAFLD comprises a disease spectrum ranging from relatively benign hepatic steatosis to more severe steatohepatitis, fibrosis, cirrhosis, and ultimately liver cancer [38]. It has become the most common form of chronic liver disease in Western countries, with a prevalence approaching 50 % of the population (already 40 % in the European Union) [39, 40]. It is estimated that NAFLD will be the number 1 indication for liver transplants in the United States in 2020 [41]. Currently, surgical treatment of coexisting NAFLD in morbidly obese patients is an evolving matter of debate [42]. A few studies propose that low levels of vitamin D may contribute to the development of NAFLD [43]. However, the mechanisms underlying the association of vitamin D and NAFLD are not yet fully understood. Recent animal studies have shown that vitamin D has an important role in the regulation of oxidative stress, the production of proinflammatory cytokines [44, 45], hepatocyte apoptosis [46], and even liver fibrosis [47]. Furthermore, NAFLD is present in approximately 90 % of bariatric patients [48, 49], and up to 5 % of these patients may have unsuspected cirrhosis [50–52]. Because NAFLD is associated with the presence of obesity, glucose and/or lipid disturbances, and arterial hypertension, it is now considered the hepatic manifestation of the metabolic syndrome.

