There are limited data on therapeutic strategies for vitamin D deficiency in bariatric patients, and procedure-specific guidelines may not be very helpful in daily clinical practice. Nevertheless, in the 2013 clinical practice guidelines [23], the American Association of Clinical Endocrinologists, the Obesity Society and American Society for Metabolic and Bariatric Surgery recommend a vitamin D supplementation of at least 3000 IU per day and to titrate to the therapeutic 25-OHD level of >75 nmol/L. This recommendation outlines the best evidence level (grade A) [23], which is based on a single randomized controlled trial done in the United States [53]. In that study, the authors attempted to find the optimal vitamin D treatment dose after surgery. Patients who had undergone RYGB were randomized to three doses of cholecalciferol: 800 IU, 2000 IU, and 5000 IU per day. The authors found that all groups had insufficient vitamin D levels at baseline and after 12 months; sufficient vitamin D concentrations were reached in only 44, 78, and 70 % of the patients in the respective groups [53]. Thus, even with very high-dose supplementation, it may be challenging to achieve normal 25-OHD levels in bariatric patients [54].

Vitamin D has multiple physiological functions beyond its classical role in calcium homoeostasis and bone metabolism, and morbidly obese persons have an increased risk for low circulating 25-OHD levels [55, 56] owing to the storage of vitamin D in adipose tissue [55].

Therefore, randomized controlled trials with vitamin D supplementation, such as the present study (Link between Obesity And Vitamin D in bariatric patients with omega-loop bypass surgery [LOAD]), are needed to establish and further pursue evidence-based and potentially optimal treatment regimens for the increasing number patients with low vitamin D status following bariatric surgery and to define more carefully the impact of specific surgical factors on vitamin D status.

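### A cheap gain in precision, not an error: the week-24 ANCOVA names only the baseline value as covariate, although body size is measured at screening and the protocol's own rationale makes it a plausible predictor of 25-OHD

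*Protocol article*

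**What the plan says.** **Analysis model.** In the Statistical analysis section, the between-group comparison after baseline is an analysis of covariance "adjusting for the baseline value as a covariate". No further covariate is named. The same section lists unadjusted tests (t, Mann–Whitney, chi-square) for comparing groups and does not tie the primary endpoint to one of these methods.

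**Randomization.** The Overview and the Randomization section give three stratification factors: 25-OHD, age and sex. Neither weight nor fat mass is among them.

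**Rationale.** The Background gives the adipose explanation twice, with different firmness. One paragraph says morbidly obese people are at risk of low 25-OHD "owing to the storage of vitamin D in adipose tissue". Another says only that the relationship "may be caused by mechanisms such as sequestration in adipose tissue" and describes the mechanisms as largely unknown.

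**Dose.** No dose depends on body size. The maintenance dose is 3420 IU per day in both arms. In the intervention arm, the second and third loading doses depend on the measured 25-OHD, for a total of 100,000 to 300,000 IU. Controls receive placebo loading.

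**Data.** Table 2 marks body weight, anthropometry and DEXA at screening.

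**The concern.** If fat stores vitamin D and the amount given does not depend on the patient's size, a larger patient should, other things equal, end with a lower week-24 25-OHD. Pre-treatment body size is then a prognostic variable for the primary endpoint. The plan collects it but neither balances it by design nor names it in the model.

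Two things are at stake, both modest. Between-patient variation that body size could explain stays in the residual and widens the confidence interval. And in a trial of 50, a chance difference in body size between the arms stays in the estimate.

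Baseline 25-OHD need not capture all of this. Eligibility cuts it off at 75 nmol/L, and a level measured before supplementation is not the same quantity as the response to supplementation.

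**Working it through.** **Inputs from the Sample size calculation section**
- Difference and SD: "Given a clinically relevant difference of 30 nmol/L and a standard deviation of 35 nmol/L of the differences".
- Two-sided alpha 0.05; "a sample size of 22 per group is needed to reach 80 % statistical power".
- Dropout 20%; "the sample size is increased to 25 per group".

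**Assumptions**
- r is the partial correlation of screening body size with week-24 25-OHD, given arm and baseline 25-OHD. The documents do not give it; the range 0 to 0.5 is used.
- The 35 nmol/L is taken as the residual SD of the baseline-adjusted model.

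**Step 1: the plan's own figure.** n per group = 2 × (1.960 + 0.842)² × 35² / 30² = 21.4, rounded up to 22. This matches the plan. The exact t-test version gives 23, which is close enough.

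**Step 2: power without the extra covariate.** At 25 per arm, SE = 35 × √(2/25) = 9.90 nmol/L. With 47 degrees of freedom (group and baseline 25-OHD fitted), power for 30 nmol/L is 84.3%, and the 95% interval half-width is 2.012 × 9.90 = 19.9 nmol/L. At 20 per arm (25 × 0.8), SE = 35 × √(2/20) = 11.07 nmol/L and power is 75.2%. The second case is illustrative: the plan speaks of imputing for dropouts, so the number analysed may not fall to 20.

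**Step 3: power with one more covariate.** The SE is multiplied by √[(1 − r²) × (1 + 1/(2n − 5))]. The second term is the average cost of estimating one more slope. One further degree of freedom is lost in the t quantile.

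For example, at n = 25 and r = 0.3: √(0.91 × 1.0222) = 0.964, so SE = 9.90 × 0.964 = 9.55 nmol/L and power is 86.8%.

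| Assumed r | Interval width ratio, 25 per arm | Power, 25 per arm | Power, 20 per arm |
|---|---|---|---|
| not fitted | 1 | 84.3% | 75.2% |
| 0 | 1.012 | 83.5% | 73.9% |
| 0.1 | 1.007 | 83.9% | 74.3% |
| 0.2 | 0.991 | 85.0% | 75.6% |
| 0.3 | 0.965 | 86.8% | 77.8% |
| 0.4 | 0.927 | 89.3% | 81.0% |
| 0.5 | 0.876 | 92.3% | 85.1% |

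**Step 4: break-even.** Setting the SE factor to 1 gives r² = 1/(2n − 4). At n = 25, r = √(1/46) = 0.15. At n = 20, r = √(1/36) = 0.17.

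**Step 5: chance imbalance.** With 25 per arm, the standardised difference between arms in an unbalanced covariate has SD √(2/25) = 0.28. At r = 0.3, an imbalance of that size moves the estimate by about 0.3 × 0.28 × 35 = 3 nmol/L, a tenth of the 30 nmol/L target. It can go either way and averages zero over randomizations.

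**The case against.** The strongest objection is that the gain is assumed. The documents give no correlation, and several of their features point to a small one:
- Baseline 25-OHD is already in the model and, on the adipose explanation, carries part of the body-size effect.
- Eligibility narrows the range: weight under 150 kg, and BMI above 40, or at least 35 with comorbidities.
- Loading in the intervention arm is titrated on 25-OHD, so patients with a poor rise receive more. That works against the correlation in that arm, though not in the control arm.
- Patients lose weight after surgery, so preoperative size may be a weak proxy for adiposity at week 24.

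All of this stands. It is why the size is shown as a range that includes a small loss.

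It can also be said that a condensed article may leave further covariates to an analysis plan that is not shown. That is fair, and it rules out calling the plan deficient. The article does, however, state the model with its covariate, so a suggestion about that model is in order.

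Three stronger readings are tempting, and the documents do not support them.
- *That every patient gets the same fixed dose.* Only the maintenance dose is common to all. What holds is that no dose is scaled to body size.
- *That the protocol names adipose storage as the established cause.* One Background paragraph is firm, but the other offers it as one possible mechanism.
- *That the primary result would be biased or the trial underpowered because of the omission.* Leaving out a prognostic covariate does not bias a randomized comparison, the usual standard error already allows for chance imbalance, and the stated 22 per group reproduces without any such covariate.

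**Conclusion.** The point holds as an optional improvement to a stated method. Adding one screening body-size covariate changes power at 25 per arm by between −1 point (r = 0) and +8 points (r = 0.5), and interval width by between +1% and −12%. A modest value such as r = 0.3 gives about 2.5 points of power and an interval 3.5% narrower. Below r of about 0.15 there is no gain. These figures rest on the planned 30 and 35 nmol/L, on reading the 35 as a baseline-adjusted residual SD, and on an assumed r. The trade is favourable because the possible loss is small and bounded, while the protocol's own rationale gives some reason to expect r above break-even. As planned, the analysis gives up some precision and leaves chance imbalance in body size uncorrected; it remains valid.

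**What to change.** Before unblinding, state that the primary week-24 comparison of 25-OHD is an analysis of covariance with group, baseline 25-OHD and screening body weight, both covariates continuous. Choose weight now rather than leaving weight and DEXA fat mass as alternatives, so that the covariate cannot be picked after the results are seen. Do not use postoperative weight: it is measured after randomization and may itself be affected by treatment.

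If the data have already been unblinded, keep the stated baseline-adjusted model as primary and report the weight-adjusted model as a sensitivity analysis, labelled as added later.

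The cost is one line of wording and one degree of freedom, with an SE about 1% wider and up to about 1 point of power lost if weight turns out not to predict the outcome. No new data are needed, and the sample size stays as it is.
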